Understanding the cost and cost-effectiveness interventions is a vital part of developing public health policy. Although there have been several studies investigating the cost-effectiveness of HCV treatment, these have nearly exclusively focused on high-income countries. Due to this, there are currently almost no studies investigating the cost or cost-effectiveness of using generic drugs for HCV treatment in LMIC, where there is a huge untreated burden.

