Cure is defined using the LLOQ, <15 IU/ml, 12 weeks after end of treatment (EOT). However, failure before this timepoint is defined using a slightly higher threshold because patients have been observed to achieve cure despite having low-level viraemia at the EOT or shortly after, and so they do not need re-treatment to achieve cure. In practice any patient with low-level viraemia <2000 IU/ml either cures or viral load rises above this level. This will be carefully reviewed by the Data Monitoring Committee. This is the same definition as used in the UK STOP-HCV-1 trial ISRCTN 37915093), where the Data Monitoring Committee has similarly reviewed individual patient viral load trajectories and has not raised any concerns.

Secondary endpoints

Secondary endpoints for the trial are

- SVR12 after the end of the combined first and any re-treatment phases (mild patients only)
- lack of initial virological response (<1 log_10_ decrease in HCV viral load from baseline)
- serious adverse events
- grade 3/4 clinical adverse events
- adverse events of any grade leading to change in treatment (SOF, DCV or any other medication)
- adverse reactions (any grade) (considered definitely/probably/possibly related to SOF or DCV)

1. Participant identification

There will be no exceptions to eligibility requirements at the time of recruitment. Questions about eligibility criteria should be addressed prior to attempting to enrol the patient – clarifications may be sought from the trial team.

The eligibility criteria are the standards used to ensure that only medically appropriate participants are considered for this study. Participants not meeting the criteria should not join the study. For the safety of the participants, as well as to ensure that the results of this study can be useful for making treatment decisions regarding other participants with similar diseases, it is important that no exceptions be made to these criteria for admission to the study.

Participants will be considered eligible for enrolment in this trial if they fulfil all the inclusion criteria and none of the exclusion criteria as defined below.

Recruitment will take place from clinics within the Hospital for Tropical Diseases in Ho Chi Minh City.

- 1. Inclusion Criteria

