**For all participants enrolled in Stratum A (mild disease) or Stratum B (cirrhosis) inclusion criteria are**

1. Aged ≥ 18 years
2. At least one detectable viraemia prior to the screening visit (by quantitative HCV RNA, qualitative assay or HCV genotype), with no intervening undetectable results
3. Plasma HCV RNA >LLOQ at screening
4. BMI >=18kg/m^2^
5. Laboratory tests: creatinine clearance (estimated using Cockcroft-Gault) >=60ml/min, international normalised ratio (INR) <1.5xULN
6. Written informed consent obtained from the patient.

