The site PI or an appropriately trained doctor must seek written informed consent from patients to enter into the trial in their own language. Individuals trained and responsible for taking consent will be documented on the trial’s Delegation Log (with signatures). Consent will be sought after explanation of the aims, methods, benefits and potential hazards of the trial and BEFORE any trial-specific procedures are performed or any blood is taken for the trial, including for the screening assessment.

The doctor taking consent must make it completely and unambiguously clear that the participant is free to refuse to participate in or withdraw from all or any aspects of the trial, at any time and for any reason, without incurring any penalty or affecting their subsequent treatment. This will be stated explicitly in the participant information sheet.

Signed consent forms must be kept by the investigator and documented in the case record form (CRF) and a copy given to the participant.

- 1. Co-enrolment Guidelines

Treatment with any other investigational product within 60 days prior to screening is an exclusion criteria, and therefore co-enrolment with a previous investigational medicinal product (IMP) trial will generally not be allowed, unless the patient is in a follow-up phase. Before enrolment into the study of a patient already participating in a previous trial (not of an investigational product), the site investigator must confirm with the investigators of the previous trial that co-enrolment is allowed. Co-enrolment in the study of patients already participating in an observational study is allowed.

1. TReatment of PARTICIPANTS

Each participant will be treated with the same drug combination (sofosbuvir 400mg and daclatasvir 60mg daily), but with differing durations of therapy. The study design is open-label; bias will be minimised by using objective laboratory measurements to determine duration of therapy and to assess treatment outcomes .

Any patient in the mild disease cohort who experiences failure of first-line treatment will initiate re-treatment as soon as possible after failure is identified. Failure of first-line treatment during the study is defined as

1. two consecutive measurements of HCV RNA > LLOQ (taken at least one week apart) after two consecutive visits with HCV RNA <LLOQ, at any time during the study follow-up period, with the latter confirmatory measurement also being >2000 IU/ml OR

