**HCV/HBV (hepatitis B virus) co-infection**

Cases of hepatitis B virus (HBV) reactivation, fatal on rare occasions, have been reported during or after treatment with direct-acting antiviral agents. HBsAg positive individulas are excluded from this study.

- - 1. **TREATMENT SCHEDULE**

The duration of SOF+DCV therapy will be determined by the Stratum the participant is in, and their response on therapy (see Figure 1). Note both SOF and DCV should always be co-administered.

- - 1. **DISPENSING**

The trial or clinic nurse will dispense SOF (and DCV) after taking the completed prescription form to the site pharmacy. All participants will receive a 28-day supply at Day 0. Further supplies will be provided at Day 28 dependent on response to therapy on Day 2 (mild disease) or Day 14 (cirrhosis). On no account should any drug assigned to a participant be used by anyone else. Unused drug must be returned to the site pharmacy immediately if a participant withdraws from treatment.

All drug dispensed at and returned to the site pharmacy should be documented on a site Accountability Log, maintained by a named person (trial pharmacist or research nurse). The designated trial pharmacist/nurse will, on receipt of supplies prior to the commencement of the trial, conduct an inventory and complete a receipt. Inventories will be conducted monthly, and logs returned to OUCRU CTU. Procedures for drug shipping, labelling, accountability, temperature monitoring and destruction will be detailed in the trial’s SOPs. OUCRU CTU will monitor drug accountability at site visits. There is no requirement for temperature monitoring of treatment packs after they are dispensed from pharmacy.

- - 1. **DRUG-DRUG INTERACTIONS**

SOF is a nucleotide prodrug, absorbed rapidly after oral administration, and cleaved into an active metabolite and inactive metabolite, GS-331007. SOF is a substrate of drug transporter P-gp and breast cancer resistance protein (BCRP) while GS-331007 is not. SOF and its metabolites can be subject to drug-drug interactions (see below) but are low risk as perpetrators of drug-drug interactions.

Medicinal products that are **potent P-gp inducers** in the intestine (i.e. rifampicin, rifabutin, St. John's wort (Hypericum perforatum), carbamazepine, phenobarbital and phenytoin) may significantly decrease SOF plasma concentration leading to reduced therapeutic effect of SOF. Co-administration with SOF is contraindicated.

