**7.2.5.B Renal impairment**

No dose adjustment of SOF is required for participants with mild or moderate renal impairment. The safety of SOF has not been assessed in participants with severe renal impairment (estimated creatinine clearance <30 ml/min/1.73 m^2^) or end-stage renal disease requiring haemodialysis. These patients are excluded from the study.

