**7.3.5.C Bradyarrhythmia**

Cases of severe bradycardia and heart block have been observed when SOF+DCV is taken with concomitant amiodarone with or without other drugs that lower heart rate. The mechanism is not established. Therefore, individuals taking amiodarone or other anti-arrhythmics (including those with permanent pacemakers) are not eligible for participation in this study. If amiodarone is required during the course of the study, SOF+DCV should be ceased immediately, and the participant closely monitored “on study, but off study drug”.

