**Pregnancy**

Pregnancy is an exclusion criterion for participation. DCV should not be used during pregnancy or in women of childbearing potential not using contraception. The potential risk to a human foetus is unknown, because there are no data from the use of DCV in pregnant women. However, studies of DCV in animals have shown embryotoxic and teratogenic effects. As pregnancy tests are performed repeatedly during the study, foetal exposure to study drugs will be limited. Furthermore, use of highly effective contraception is recommended throughout the trial and for 5 weeks after completion of DCV therapy. Any participant who becomes pregnant on study must be counselled appropriately on the risks of DAA exposure to the unborn child, taking into account the duration of DAAs received.

- 1. Adherence

As the intervention will start immediately following enrolment, suitable participant information and fully informed consent procedures will ensure that participants understand the trial requirements. Therefore, any non-adherence will likely be a consequence of the intervention itself (e.g. drug intolerance or toxicity) which would also be likely to occur if it were incorporated within clinical practice, i.e. non-adherence will likely be part of the strategy being evaluated. The intention-to-treat analysis will therefore incorporate the level of non-adherence as would be anticipated in general clinical practice. Non-adherence will be assessed using participant self-report and pill counts.

- 1. Treatment Data Collection

See Trial Assessment Schedule

- 1. Non-trial Treatment

As this is a pragmatic trial, decisions regarding all other medications taken by the participant will be determined by the attending physician according to the clinical circumstances.

- - 1. **Treatment After end of study drug**

The treatment of participants after the study finishes should be determined by the local physician responsible for care and in line with national guidance. Normal standards of clinical care should be followed with careful documentation of their management in the CRF.

1. Safety Reporting

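### Section 7.6 bars daclatasvir for women of childbearing potential who use no contraception, but the eligibility criteria exclude only current pregnancy, although every participant takes daclatasvir

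*Protocol*

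**What the plan says.** The Pregnancy paragraph of section 7.6 (Protocol Treatment Discontinuation) restricts the drug: "DCV should not be used during pregnancy or in women of childbearing potential not using contraception". It gives as reasons the absence of human pregnancy data and embryotoxic and teratogenic findings in animals. It then relies on repeated pregnancy tests to limit foetal exposure. It recommends highly effective contraception during the trial and for 5 weeks after daclatasvir ends.

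Section 5 gives the drug to everyone: "Each participant will be treated with the same drug combination (sofosbuvir 400mg and daclatasvir 60mg daily", with only the duration differing. Section 7.7 (Adherence) says the intervention begins immediately after enrolment.

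Section 3 makes the listed criteria decisive. People are "eligible for enrolment in this trial if they fulfil all the inclusion criteria and none of the exclusion criteria" given there, and "There will be no exceptions to eligibility requirements at the time of recruitment". The only listed item that bears on pregnancy is exclusion 12, which is current pregnancy.

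**The concern.** Section 7.6 makes contraception a condition for using daclatasvir in women who could conceive, but section 3 does not make it a condition of entry. Because all participants take daclatasvir from the outset, a condition of use that applies at the first dose is in effect a condition of entry and belongs in the list that decides entry.

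The paragraph is also uneven in strength. It first says the drug should not be used without contraception, and then only recommends contraception of the highly effective kind. A site could reasonably be unsure whether contraception is mandatory.

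What is at stake is avoidable foetal exposure to a drug that the protocol itself describes as teratogenic in animals. Pregnancy testing finds a pregnancy after conception and does not prevent one.

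**Working it through.** The plan gives no figure to reproduce. The check is an item-by-item reading of the eligibility lists against the restriction in section 7.6.

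**Eligibility items read**

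| List | Items | Mention contraception or childbearing potential | Mention pregnancy |
|---|---|---|---|
| Common inclusion criteria (3.1) | 6 | 0 | 0 |
| Additional for Stratum A (3.1) | 2 | 0 | 0 |
| Additional for Stratum B (3.1) | 3 | 0 | 0 |
| Exclusion criteria (3.2) | 14 | 0 | 1 (item 12) |
| Total | 6 + 2 + 3 + 14 = 25 | 0 | 1 |

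**Could a general item cover the case?** Four exclusions come closest:

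- Item 4 concerns life expectancy.
- Item 5 concerns ability to adhere to the trial regimen.
- Item 8 concerns interacting medication for which a dose adjustment would be recommended.
- Item 14 concerns ability to attend follow-up.

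None of them reaches a healthy, adherent woman who uses no contraception.

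**Putting the sections together**

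1. Take a non-pregnant woman of childbearing potential who uses no contraception and meets the criteria on age, viraemia, BMI, laboratory values, consent, genotype and liver stage.
2. Under section 3 she meets all inclusion criteria and no exclusion criterion, so she is eligible.
3. Under sections 5 and 7.7 she would start daclatasvir immediately after enrolment.
4. Under section 7.6 she should not be given daclatasvir.

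Steps 2 and 4 do not match, and no visible text resolves the mismatch before enrolment.

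**Length of the period a criterion would cover.** This is planned treatment weeks (section 5.1) plus the 5 weeks named in section 7.6:

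- Stratum A: 4 + 5 = 9 weeks, or 8 + 5 = 13 weeks.
- Stratum B: 12 + 5 = 17 weeks, or 24 + 5 = 29 weeks.
- Re-treatment (mild disease only; 12 weeks according to section 13.2.1): a further 12 + 5 = 17 weeks from its start.

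Follow-up after treatment is 12 weeks (section 6.1). Since 5 < 12, the post-treatment part falls within scheduled follow-up and needs no extra visits. These figures describe how long the requirement lasts, not the risk of pregnancy. The number of women concerned cannot be derived, because the protocol gives neither the expected sex and age mix nor contraceptive use.

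**The case against.** The strongest reply is that the two sections can both be obeyed. Section 3 forbids waiving criteria to admit someone who fails them. It does not oblige a site to dose everyone who passes, and section 7.6 is itself an instruction to the prescriber. This stands: a reader might infer that the protocol orders a site to treat such a woman, and the text does not say that. What remains is that she could be enrolled and only then found unsuitable for a drug that every participant takes at once.

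A second reply is that the wording draws a deliberate line. Where section 7 means an eligibility bar it says so, for example "HBsAg positive individulas are excluded from this study", "These patients are excluded from the study" and "individuals taking amiodarone or other anti-arrhythmics (including those with permanent pacemakers) are not eligible for participation in this study". The contraception sentence speaks of use, and contraception can be started before dosing. That is a fair reading, but with no gap between enrolment and first dose the distinction has no room to operate.

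Third, the missing pages may deal with it. The tables of Appendix II, the schema and the consent pages are not shown. Pregnancy tests are evidently scheduled, and the abbreviation list defines WOCBP, a term the visible text does not otherwise use. This stands as a limit: one cannot claim that screening staff would never be prompted to ask. It does not alter the lists in sections 3.1 and 3.2.

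Two further inferences are tempting and not supported:

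- **That contraception is the only section 7 restriction left out of section 3.** It is not. Sections 7.2.4 and 7.3.4 advise against or contraindicate enzyme and transporter inducers, and exclusion 8, read literally, covers only drugs calling for a dose adjustment.
- **That the protocol fails to stop treatment when a participant becomes pregnant.** A stop follows from the section 7.6 sentence, and sections 7.3.5.F and 7.6 then require sofosbuvir to stop as well.

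**Conclusion.** The point holds as an inconsistency between sections 3 and 7.6 that bears on patient safety. A woman of childbearing potential using no contraception satisfies all listed criteria for a trial in which everyone receives a drug that section 7.6 says she should not be given. None of the 25 listed criteria addresses contraception.

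Its size is modest. The number affected is unknown, and repeated pregnancy testing reduces the risk without removing it. The endpoint, sample size and analysis do not change. The conclusion assumes that the eligibility lists as shown are complete, which their numbering and content support, and that any contraception check in the pages not shown is not itself an entry criterion.

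This is a cheap improvement on patient-safety grounds. It does not show that the trial is unsafe or that its results would be biased.

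**What to change.** Make two edits:

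1. In section 3, add a criterion that women of childbearing potential must agree to use effective contraception while taking daclatasvir, including during any re-treatment, and for 5 weeks after the last daclatasvir dose.
2. In the Pregnancy paragraph of section 7.6, state that contraception is required for that same period. Keep the existing recommendation of highly effective contraception throughout the trial as it is.

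The mandatory period need not extend to the whole of follow-up. Section 7.6 only recommends contraception for that longer span, and its condition on daclatasvir use would apply again if re-treatment began.

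The cost is a short amendment with matching wording in the participant information, and possibly a few women who become ineligible. No statistical section needs to change.

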The principles of ICH GCP require that both investigators and sponsors follow specific procedures when notifying and reporting adverse events or reactions in clinical trials. These procedures are described in this section of the protocol. [Section 8.1 - Definitions](#Definitions) lists definitions, [Section 8.2 – Investigator Responsabilites](#InvestigatorResponsibilities) gives details of the investigator responsibilities*.*

- 1. Definitions

The principles of ICH GCP apply to this trial protocol, as per Table 1: Definitions below.

*Table 1: Definitions*

| *Table* | *Definition* |
| --- | --- |
| Adverse Event (AE) | Any untoward medical occurrence in a participant or clinical trial subject to whom an investigational medicinal product has been administered including occurrences that are not necessarily caused by or related to that product. |
| Adverse Reaction (AR) | Any untoward and unintended response to an investigational medicinal product related to any dose administered. |
| Unexpected Adverse Reaction (UAR) | An adverse reaction, the nature or severity of which is not consistent with the information about the investigational medicinal product in question set out in the Summary of Product Characteristics (SPC) for that product. |
| Serious Adverse Event (SAE) or Serious Adverse Reaction (SAR) or Suspected Unexpected Serious Adverse Reaction (SUSAR) | Respectively any adverse event, adverse reaction or unexpected adverse reaction that:   - Results in death - Is life-threatening* - Requires hospitalisation or prolongation of existing hospitalisation** - Results in persistent or significant disability or incapacity - Consists of a congenital anomaly or birth defect - Is another important medical condition*** |

*The term life-threatening in the definition of a serious event refers to an event in which the participant is at risk of death at the time of the event; it does not refer to an event that hypothetically might cause death if it were more severe, for example, a silent myocardial infarction.

**Hospitalisation is defined as an inparticipant admission, regardless of length of stay, even if the hospitalisation is a precautionary measure for continued observation. Hospitalisations for a pre-existing condition (including elective procedures that have not worsened) do not constitute an SAE.

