*** Medical judgement should be exercised in deciding whether an AE or AR is serious in other situations. The following should also be considered serious: important AEs or ARs that are not immediately life-threatening or do not result in death or hospitalisation but may jeopardise the subject or may require intervention to prevent one of the other outcomes listed in the definition above; for example, a secondary malignancy, an allergic bronchospasm requiring intensive emergency treatment, seizures or blood dyscrasias that do not result in hospitalisation or development of drug dependency*.*

Adverse Events include:

- An exacerbation of a pre-existing illness
- An increase in frequency or intensity of a pre-existing episodic event or condition
- A condition (even though it may have been present prior to the start of the trial) detected after trial drug administration
- Continuous persistent disease or a symptom present at baseline that worsens following administration of the study treatment
  - 1. **Medicinal Products**

An investigational medicinal product is defined as the tested investigational medicinal product (IMP) and the comparators used in the study. This therefore includes:

- daclatasvir
- sofosbuvir

Adverse reactions include any untoward or unintended response to drugs. Reactions to an IMP or comparator should be reported appropriately.

- - 1. **Exempted Adverse Events**

In the context of this trial Adverse Events **do not include**:

- Medical or surgical procedures; the condition that leads to the procedure is the adverse event
- Pre-existing disease or a condition present before treatment that does not worsen
- Hospitalisations where no untoward or unintended response has occurred, e.g. elective cosmetic surgery, social admissions
- Overdose of medication without signs or symptoms
- Disease-related events that are not fatal
  1. Investigator Responsibilities

All clinical grade 3 or 4 AEs, serious AEs, and all ARs, whether expected or not, should be recorded in the CRF. Non-serious grade 1 or 2 AEs and laboratory grade 3 or 4 AEs are only reported if they lead to a change or interruption in treatment (SOF, DCV or any other medication being taken by the participant).

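### Section 8.1.2 exempts undefined non-fatal disease-related events from being adverse events, contradicting Section 8.1 and Table 2, so capture of non-fatal liver events judged unrelated to treatment is uncertain

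*Protocol*

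**What the plan says.** Section 8.1 closes with a list of what adverse events include. Two entries concern disease already present at entry: "An exacerbation of a pre-existing illness" and "Continuous persistent disease or a symptom present at baseline that worsens following administration of the study treatment".

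Section 8.1.2 then gives the exemptions. It opens with "In the context of this trial Adverse Events" and sets out what these leave out. One exemption covers pre-existing disease, but only where it has not worsened. The last is "Disease-related events that are not fatal". The protocol does not define disease-related, makes no exception for serious or high-grade events, and does not confine the item to one stratum.

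Table 1 in Section 8.1 makes seriousness a property of an existing event: "Respectively any adverse event, adverse reaction or unexpected adverse reaction that" meets one of the listed criteria. Section 8.2.1 likewise has the investigator assess seriousness once an AE or AR has occurred. Table 2 in the same section grades causality. An event for which the participant's clinical condition is a reasonable alternative explanation is graded unlikely and classed as an unrelated SAE.

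Section 2.2 lists four safety endpoints. Three are built on adverse events: "serious adverse events", "grade 3/4 clinical adverse events" and "adverse events of any grade leading to change in treatment (SOF, DCV or any other medication". The fourth is adverse reactions of any grade. Section 3.3 plans 103 participants, 43 of them in Stratum B with compensated cirrhosis.

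**The concern.** In a stratum made up entirely of people with cirrhosis, a non-fatal decompensation is both a foreseeable serious event and, on any ordinary reading, a disease-related one. Taken at its word, the last exemption says that such an event is not an adverse event at all. The neighbouring text says that it is. An investigator can follow either in good faith, so the same event could be reported for one participant and not for another.

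At stake are the completeness and consistency of the safety endpoints in Stratum B. Section 2.2 has no separate liver-event endpoint that would pick up what the adverse-event route misses; its other endpoints are virological. The rule governs what sites report, so it takes effect before any analysis. A statistical analysis plan cannot restore events that sites were told not to report.

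**Working it through.** No sample size, power or error rate is involved. The check follows one event through the protocol's definitions.

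**Test case.** A Stratum B participant has a non-fatal decompensation that leads to hospital admission. The investigator judges it unrelated, or unlikely to be related, to SOF or DCV.

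| Place in the protocol | What it implies for the test case |
|---|---|
| 8.1, list of what AEs include | An AE: baseline disease has worsened |
| 8.1.2, exemption for pre-existing disease | Not exempt: it covers only disease that has not worsened |
| 8.1.2, last exemption | Not an AE: disease-related and not fatal |
| 8.2.1, Table 2 | An unrelated SAE: explained by the clinical condition |

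Three places point to capture and one to exclusion. The excluding text comes after the general list and is framed as specific to this trial, so a reader could reasonably give it priority. The protocol states no order of precedence.

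**If the last exemption is followed:**
1. The event is not an AE.
2. Judged unrelated or unlikely, it is not an AR either.
3. Under Table 1 it therefore cannot be an SAE, and the 24-hour notification in Section 8.2 does not apply.
4. It is also not a grade 3/4 clinical AE, nor an AE leading to a change in treatment.
5. It is absent from three of the four safety endpoints in Section 2.2.

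**If the event is judged possible, probable or definite:** it is an adverse reaction, defined separately in Table 1. Sections 6.3 and 8.2 send every such reaction to the CRF whatever its grade, it counts in the fourth safety endpoint, and if serious it is an SAR with the same 24-hour notification. Fatal events fall outside the exemption by its own wording.

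The possible loss is therefore confined to non-fatal events judged unrelated or unlikely.

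**Scale.** Inputs from Section 3.3: 43 participants in Stratum B, 103 in total.
- Share of the trial with cirrhosis: 43/103 = 41.7%. This is the population exposed to the ambiguity, not a measure of harm.
- Effect of one affected participant with no other recorded SAE: 1/43 = 2.3 percentage points on the Stratum B SAE proportion, and 1/103 = 1.0 point on the whole-trial proportion.
- Number of events affected: not computable. It would need the rate of non-fatal liver events, the share judged unrelated or unlikely, and the share of investigators who apply the exemption. The protocol gives none of these.

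**The case against.** The strongest defence is that the protocol read as a whole intends to capture these events. The inclusion list counts worsening disease, the neighbouring exemption stops where disease worsens, Table 2 has a category for serious events caused by the participant's condition, and Section 8.2.2 places foreseeable, predefined SAEs in the annual ethics report, which presupposes that they are SAEs. Much of this stands. It rules out the stronger reading, that the protocol plainly removes all non-fatal liver events. It does not settle the matter, because the contrary instruction remains in the text.

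The adverse-reaction route also stands. Table 2 asks only for some evidence, such as timing, to grade an event possible, so many events during dosing could be captured that way. But the trial has a single arm and is open label. Whether an event is due to disease or to drug rests on the investigator's judgement without a comparator, and events judged unrelated are the ones exposed.

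It may be said that exempting disease-related events is common practice. That is defensible where such events are collected by another route, and the text at hand shows none as an endpoint. Ultrasound and AFP at entry, end of treatment and 12 weeks later give some liver surveillance, but they do not feed the adverse-event endpoints.

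A reader might infer three further things that the documents do not support:
- **A number of lost events**, from applying an assumed rate to the 43. The inputs are missing.
- **A comparable gap for hepatitis flares in Stratum A.** Viral rebound there is followed by twice-weekly viral loads after treatment and enters the primary endpoint. A purely laboratory flare falls under the separate laboratory reporting rule in Section 8.2.
- **That the DMC would not see a liver signal.** Section 14.2 has it review accumulating data under a charter that is not at hand, and nothing limits it to adverse-event forms.

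**Conclusion.** The point holds as an unreconciled contradiction. Sections 8.1 and 8.1.2 and Table 2 give opposite answers on whether a non-fatal disease-related event is an adverse event. Non-fatal liver events in the 43 Stratum B participants, if judged unrelated or unlikely to be related, could go unrecorded in three of the four safety endpoints and escape 24-hour notification, depending on which text the investigator follows. The documents do not show that such events would all be missing.

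The number affected cannot be computed. In a stratum of this size each one matters, at 2.3 percentage points per participant. The primary endpoint is untouched. The change should be made because the defect lies in event collection and cannot be corrected at analysis.

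This rests on the text at hand. The Appendix II schedule tables are not shown, so a dedicated liver-event form cannot be excluded. Even if one existed, the definitions would still conflict.

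**What to change.** Reconcile Sections 8.1 and 8.1.2 in one of two ways.

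1. Delete the last item of Section 8.1.2. This is the simpler course, because Section 8.2 already keeps non-serious grade 1 or 2 adverse events off the CRF unless they lead to a change or interruption in treatment or are reactions.
2. Keep the item but limit it to a defined list of non-serious, grade 1 or 2 disease-related events. State that any serious event, any grade 3/4 clinical event and any hepatic decompensation remains an AE or SAE whatever its attributed cause. Say also how a listed event that leads to a change in treatment is handled, since that is an endpoint of its own.

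Under either option, check the footnote to Table 1 on admissions for pre-existing conditions, so that it cannot be read as excluding an admission for worsened cirrhosis.

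The cost is a short protocol amendment, a note to the site and a few more event forms, with 24-hour notification to the trials unit for those that are serious. Expedited reporting to the ministry ethics committee need not grow: Section 8.2.2 already moves foreseeable, predefined SAEs to the annual report, provided the events concerned are named as such.
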